## Abstract

**Background:**

The optimal criteria to diagnose gestational diabetes mellitus (GDM) remain contested. The Swedish National Board of Health introduced the 2013 WHO criteria in 2015 as a recommendation for initiation of treatment for hyperglycaemia during pregnancy. With variation in GDM screening and diagnostic practice across the country, it was agreed that the shift to new guidelines should be in a scientific and structured way. The aim of the Changing Diagnostic Criteria for Gestational Diabetes (CDC4G) in Sweden (www.cdc4g.se/en) is to evaluate the clinical and health economic impacts of changing diagnostic criteria for GDM in Sweden and to create a prospective cohort to compare the many long-term outcomes in mother and baby under the old and new diagnostic approaches.

**Methods:**

This is a stepped wedge cluster randomised controlled trial, comparing pregnancy outcomes before and after the switch in GDM criteria across 11 centres in a randomised manner. The trial includes all pregnant women screened for GDM across the participating centres during January–December 2018, approximately two thirds of all pregnancies in Sweden in a year. Women with pre-existing diabetes will be excluded. Data will be collected through the national Swedish Pregnancy register and for follow up studies other health registers will be included.

**Discussion:**

The stepped wedge RCT was chosen to be the best study design for evaluating the shift from old to new diagnostic criteria of GDM in Sweden. The national quality registers provide data on the whole pregnant population and gives a possibility for follow up studies of both mother and child. The health economic analysis from the study will give a solid evidence base for future changes in order to improve immediate pregnancy, as well as long term, outcomes for mother and child.

**Trial registration:**

CDC4G is listed on the ISRCTN registry with study ID ISRCTN41918550 (15/12/2017)

## Background

Hyperglycaemia during pregnancy is a growing problem globally and is associated with several long- and short-term adverse outcomes for the mother and offspring [1–5]. In particular, maternal hyperglycaemia induces foetal hyperinsulinemia with enhanced foetal growth and increased risk of foetuses being born large for gestational age (LGA). The rate of macrosomia, neonatal hypoglycaemia and caesarean delivery increase linearly with increasing levels of maternal hyperglycaemia [6]. Women with GDM are also at higher risk of gestational hypertension and preeclampsia. In the long term, metabolic diseases such as Type 2 diabetes mellitus (T2DM), cardiovascular disease and obesity are more frequent among women with prior GDM [2, 7–9] . In offspring GDM has been shown to be associated with adiposity and risk for prediabetes [3, 4, 10, 11]. Treatment of GDM involves dietary and physical activity advice, blood glucose monitoring, and where necessary metformin or/and insulin therapy. GDM management has been shown to reduce maternal and perinatal morbidity [12–14].

Internationally, the prevalence of GDM varies from 1 to 28% depending on the ethnic composition and prevalence of T2DM of the background population, local GDM screening strategies and diagnostic criteria [15–17]. This variation in screening and diagnostic approaches has made global comparisons of GDM prevalence and outcomes problematic. In order to progress towards a universal standard approach to GDM diagnosis, the World Health Organisation (WHO) recommended in 2013 that a 2-h 75 g oral glucose tolerance test (OGTT) should be used, with three time points blood testing (fasting, 1- and 2-h) [1]. These 2013 WHO criteria define GDM as ≥5.1, ≥10.0 and/or ≥ 8.5 mmol/L fasting, 1-h and/or 2-h thresholds. These cut-off values are based on a ≥ 75% adjusted excess risk of adverse neonatal outcomes (e.g. large for gestational age (LGA), foetal hyperinsulinemia), based on data from the Hyperglycaemia and Adverse Pregnancy Outcomes (HAPO) study involving 25,505 women from nine countries [18]. There has been debate over the merits of these new criteria as the number of women diagnosed with GDM would be expected to increase by 15–30%, raising concerns over their cost and clinical effectiveness [19–22]. While the thresholds are based upon calculated excess risk, the decision to base the diagnostic criteria on ≥75% excess risk was based upon consensus. Some countries (e.g. Canada, Norway) have reduced GDM numbers by using thresholds based upon a ≥ 100% excess risk of adverse neonatal outcomes (5.3- and/or 10.6- and/or 9.0 mmol/L, respectively) [23, 24]. Others have not based their criteria on HAPO data at all (e.g. England, New Zealand).

Older Swedish GDM criteria are based on varying cut-off values. If a fasting threshold was used (not used in one region), then ≥7.0 mmol/L was considered GDM. The 2 h criteria ranged from 9.0–11.1 mmol/L, using either capillary or venous samples. Using these criteria, 1–3% of the 115, 000 births were complicated by GDM annually. In June 2015, following a review of the available evidence, the Swedish National Board of Health and Welfare (SNBHW) recommended a move to the 2013 WHO diagnostic criteria, using venous sampling. The SNBHW made no recommendations in relation to the screening (e.g. universal vs risk factor).

With the current variation in GDM screening/diagnostic practice across Sweden [25], and the debate over the criteria, there was a recognition that the transition to the recommended new guidelines could be either by an ad hoc, or planned and structured way, to minimise clinical variation. National registers in Sweden offer a possibility to assess the impact of introducing the new GDM criteria on pregnancy outcomes and long-term health for both mother and child. A stepped wedge cluster randomised controlled trial (SW-CRCT) was the most realistic approach to evaluate this change on a national level [26–30]. A SW-CRCT involves randomly allocated times for clusters to introduce an intervention, allowing participants before and after any change to serve as control and intervention groups respectively. Reasons for choosing this study design were:
The intervention is a change in one clinical routine in a population, making it unrealistic to randomise by individual.All sites were to end with adopting the national guidelines as promptly as possible, which would have been delayed using a simple case control approach.Roll out in one go, across multiple centres was unrealistic, making a parallel cluster randomised controlled trial unrealistic. Steady adoption, site by site, was seen as the best way to make the change in the most organised manner.

This study will provide evidence to help address some of the clinical controversies over GDM diagnosis. Our aim is to test whether there is a reduction in adverse neonatal and maternal outcomes following the implementation of the new GDM criteria, and to evaluate the health economic impact on a population level.

Our specific objectives are:
To compare the rates of LGA and other adverse neonatal and maternal pregnancy outcomes before and after the change in GDM diagnostic criteria.To compare the health care costs before and after the change and assess the net costs/savings.To create prospective cohorts to compare the long-term outcomes in mothers and offspring exposed to the old and new diagnostic approaches.

## Methods

### Study design

The Changing Diagnostic Criteria for Gestational diabetes (CDC4G) in Sweden study is a national prospective, unblinded, SW-CRCT of the switch from the former Swedish diagnostic criteria to the WHO 2013 criteria for GDM i.e. to the 3 point OGTT with fasting plasma glucose, 1-h and/or 2-h diagnostic thresholds of ≥5.1, ≥10.0, ≥8.5 mmol/L, respectively (Fig. 1). Each participating centre constitutes one cluster, in which the patients continue to undergo screening for GDM following their usual approach, see Table 1. The time of transition to the new criteria is randomised and subsequently rolled out until all 11 clusters (i.e. centres) implement the new GDM regimes during 2018, see Fig. 2. The transition necessitated the introduction of a fasting glucose sample in one region, and a 1-h sample across all 11 regions. This means that a total population evaluation of the change is required, as many women with GDM diagnosed by the new criteria, will not be identified during the control period (e.g. those without the 1-h test). A sub-analysis among those with untreated and treated GDM by the WHO 2013 is also planned.

**Fig. 1 Fig1:**
[figure not shown]
Time of preparation, set up, control and intervention in the CDC4G study during 2017, 2018 and 2019. Q = quartile, 3 months period

**Table 1 Tab1:** List of included regions and methods for diagnosing GDM

Centres	Number of births 2017^a^	Indication for a diagnostic OGTT									Diagnostic criteria prior to switch (mmol/L)	Method for glucose analysis
		Previous				BMI at booking	FH^d^	Polyhyd ramnios	Accelerated fetal growth	RPG		
		GDM	Macro somia^b^	LGA^c^	Stillbirth							
1. Stockholm	28,602	T1 & 24–28	24–28			≥35		Yes	Yes	RPG^e^ ≥ 9 mmol/L at booking, week 25, 29, 32/33, 37/38.	FPG < 7.0 and 2-h PG 8.9–11.1	Roche Cobas Beckman Coulter Au. Siemens Advia (hexokinase)
2. Örebro	3565	24–28	24–28			≥35	24–28	Yes	Yes-within 3 days	RPG^e^ ≥ 9 mmol/L at booking, week 24, 28/29, 33, 37.	FPG < 7.0 and 2-h PG 8.9–11.0	Siemens Advia (hexokinase)
3. Västmanland	3120	24–28	24–28			> 35		Yes	Yes	RPG^e^ ≥ 9.0 mmol/L at booking week 25, 30, 35.	FPG < 7.0 and 2-h PG 8.9–11.	Beckman Coulter Au (hexokinase)
4. Dalarna	3232	12–14/24–28	24–28	24–28		> 35	24–28	Yes	Yes	RPG^e^ ≥ 9.0 mmol/L at booking, week 24, 28/29, 33, 37.	FPG < 7.0 and/or 2-h PG 8.9–11.1	Siemens Advia (hexokinase)
5. Uppsala	4200	12–14/24–28	24–28	24–28		≥35	24–28	Yes	Yes	RPG^e^ ≥ 8.8 mmol/L at booking, week 25, 28/29, 33, 37	FPG ≥7.0 and/or 2-h PG ≥10.0	Abbott Architect (hexokinase)
6. Göteborg	9550	25–29	25–29	25–29		≥35	25–29	Yes	(Yes)	Within 1 week if RPG^e^ 8.0–12.1 mmol/L at first antenatal care visit, week 25, 28–29, 35–36.	FPG ≥7.0 and/or 2-h PG ≥10.0 RPG^c^ ≥ 12.2	Nova Biomedical StatStrip TM Multi-Well™ (glucose oxidase)
7. Gotland	538	24–28	24–28		24–28	≥35	24–28	Yes	Yes	RPG^e^ ≥ 9.0 mmol/L at enrollment week 25, 29, 32/33, 37/38.	FPG < 7.0 and 2-h PG 8.9–11.0	HemoCue AB HemoCue 201 RT (glucose dehydrogenase)
8. Halland	4446	12/ 24–28		24–28	24–28	≥30	24–28	Yes	Yes	RPG^e^ ≥ 8.0 mmol/L at enrollment, week 12, 28/29, 32, 37	FPG < 7.0 and 2-h PG 9.0–11.1	HemoCue AB HemoCue 201 RT (glucose dehydrogenase)
9. Malmö	4944	10–12	10–12			≥35	10–12	Yes	No	Capillary 75 g OGTT week 28 in all women. FPG^e^ ≥ 7 and/or 2-h PG^e^ ≥ 10.0 mmol/L indication for a diagnostic OGTT	FPG ≥7.0 and/or 2-h PG ≥9.0	Roche Cobas (hexokinase)
10. Lund	3703	10–12	10–12			≥35	10–12	Yes	No			
11. Kristianstad	2085	10–12	10–12			≥35	10–12	Yes	No			

Legend: When not otherwise stated, glucose measurement is based on venous plasma

*BMI* body mass index, *FH* family history, *FPG* fasting plasma glucose, *IUFD* intrauterine fetal death, *LGA* large for gestational age, *OGTT* oral glucose tolerance test, *PG* plasma glucose, *RPG* random plasma glucose, *T1* trimester 1

^a^Number of births per year based on data from the Swedish Medical Birth register year 2017

^b^Defined as birth weight ≥ 4.5 kg

^c^Defined as birth weight ≥ + 2 standard deviations above the Swedish reference curve [31]

^d^In Dalarna, Malmö, Lund, Kristianstad, Uppsala, Gotland, Halland defined as first degree relative with type 1 or type 2 diabetes, otherwise first degree relative with type 2 diabetes

^e^Based on capillary samples

**Fig. 2 Fig2:**
[figure not shown]
CONSORT 2010 flow diagram of the stepped wedge cluster randomised CDC4G - trial

Sites have previously varied in how samples were taken, with some using capillary and some venous sampling. As venous sampling was used in the HAPO study, and is the approach recommended by the SNBHW and the WHO, all study centres using capillary sampling for diagnosing GDM changed to venous during the national preparation period (September–December 2017). GDM clinical management has also varied across the country and new guidelines for GDM treatment and obstetric surveillance were introduced during the national preparation period, prior to the commencement of the trial. It was agreed that no local policy should change over the trial period.

The trial was performed within the Swedish Network for Clinical Studies within Obstetrics and Gynaecology (SNAKS; www.sfog.se).

#### Participants

All regions in Sweden were invited to participate over the 12-month study period. Eleven (65–67,000 birth/year) out of 21 regions in Sweden agreed to participate. All women within the participating regions (including within both primary and secondary care) across Sweden are included in the study, unless they opt out from the national register. Women with pre-existing diabetes are excluded. This approach, to use de-identified data from the national registers, without individual consent, was approved by the Uppsala Regional Ethics committee on behalf of all Research Committees across Sweden. The national SPR uses an opt out approach, with less than 100 opts out yearly.

#### Outcomes

The primary outcome is LGA (birth weight above the 90th percentile for gestational age and sex using centile tables) based on Swedish reference population (twins, major malformations and intrauterine deaths excluded from reference population). This is the only common pregnancy outcome shown to be substantially and consistently reduced by treating GDM [32].

Secondary outcomes for neonate and mother are listed in Table 2.

**Table 2 Tab2:** Outcomes, sampling and measurements

			Data collection points		
	Method	Sources	Baseline	During pregnancy	Birth/postpartum
Primary Outcome					
LGA^a^	scale	SPR^b^			x
Secondary maternal outcomes					
Gestational Hypertension	Blood pressure or ICD code	SPR^b^/ eCRF^f^		x	x
Pre-eclampsia	ICD code	SPR^b^		x	x
Shoulder dystocia	ICD code	SPR^b^			x
Induction of labour	ICD code	SPR^b^			x
Emergency LSCS	ICD code	SPR^b^			x
Elective LSCS	ICD code	SPR^b^			x
Instrumental delivery	ICD code	SPR^b^			x
Length of maternal stay from delivery to discharge	hours, days	SPR^b^			x
Perineal trauma-3 and 4 degree	ICD code	SPR^b^			x
Breastfeeding at hospital discharge	Yes/no	SPR^b^			x
Maternal HbA1c (mmol/mol)	Blood sample	eCRF^f^	x	x	
Self-reported health	Scale 1–6	SPR^b^		x	x
Satisfaction with childbirth	Scale 1–10	SPR^b^			x
Post-part bleeding	ml	SPR^b^			x
Gestational weight gain	g or kg	SPR^b^	x	x	
Secondary neonatal outcomes					
Stillbirth (≥22 + 0)	ICD code	SPR^b^/SNQ^c^			x
Neonatal death (< 28 days)	ICD code	SPR^b^ /SCB^d^			x
Erbs palsy	ICD code	SPR^b^/SNQ^c^			x
Metabolic acidosis^g^	Umbilical artery and venous blood sample	SPR^b^			x
1,5,10 min Apgar score < 4	Clinical examination	SPR^b^			x
Hypoxic ischemic encephalopathy I-III	ICD code	SPR^b^/SNQ^e^			x
Intracranial haemorrhage	ICD code	SPR^b^/SNQ^e^			x
Meconium aspiration syndrome	ICD code	SPR^b^/SNQ^e^			x
Mechanical ventilation		SPR^b^/SNQ^e^			x
Fractured clavicle/humerus	ICD code	SPR^b^/SNQ^e^			x
Blood glucose in the infants (mmol/L)	Blood sample	eCFR^f^			x
Preterm birth < 37, 34 or 32 weeks	ICD code	SPR^b^			x
NICU date	(xxxx/yy/zz)	eCRF^f^			x
NICU days	days	eCRF^f^/SPR^b^			x
SGA^h^	Calculated from birth weight / gestational age/gender	SPR^b^			x
Bilirubin (highest value)	Blood sample	eCRF^f^			x
Phototherapy	Medical record	eCRF^f^			
Hypoglycaemia needing IV therapy		eCRF^f^			x
Supplementary feeding					
Supplementary feeding indication	Medical record	eCFR^f^			x
Interval (hours) and volume (ml) of supplementary feeding		eCFR^f^			x
Product used		eCFR^f^			x
Use of dextrose gel or intravenous treatment		eCFR^f^			x

^a^ Large for Gestational Age: Birth weight above the 90th percentile for gestational age in the Swedish reference population corrected for gestational age and gender

^b^ Swedish pregnancy register: Diagnosis based on ICD codes or values (ml, kg, g, numbers). Variable list available on https://www.medscinet.com/gr/forskare.aspx

^c^ The Swedish National Patient Register

^d^ Statistics Sweden

^e^ Swedish Neonatal Quality Register

^f^ eCFR.www.medscinet.com

^g^ pH < 7.05 and BE > 12 mmol/L or pH < 7.0

^h^ Birth weight < 10th percentile for gestational age, corrected for gestational age and gender. Swedish reference population

A healthcare cost-utility analysis will be undertaken.

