As the randomisation is on the cluster level and not on the participant level, we will adjust for important prognostic predictors for LGA, such as chronic hypertension, mother’s age, BMI, country of mother’s birth and the mother’s smoking behaviour during pregnancy. Stratification with interaction tests by prognostic factors will be used to further investigate if the associations with LGA between the two diagnostic criteria are heterogeneous and the new diagnostic criteria have an even larger impact in some subgroups according to risk factors.

Because of the stepped wedge study design, some recommended design-specific analyses will be conducted such as stratification by time period to evaluate if the intervention association with outcomes are homogenous during the study time period, or heterogeneity within centres between the two interventions. The secondary adverse neonatal and maternal outcomes will be analysed using the same type of methods and considerations as for the primary outcome. A sub-analysis will be conducted comparing those with fasting glucose 5.1–6.9 mmol/L and/or 2-h glucose 8.5–8.9 mmol/L before and after the switch in criteria.

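### The metabolic acidosis definition (Table 2, footnote g) gives base excess the wrong sign; coded literally on signed values, it reduces to pH < 7.0

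*Protocol article*

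**What the plan says.** In the protocol article (Methods, Outcomes), Table 2 has a row "Metabolic acidosis^g" among the secondary neonatal outcomes. The method given is "Umbilical artery and venous blood sample" and the source is the Swedish Pregnancy Register. Footnote g supplies the case rule: "pH < 7.05 and BE > 12 mmol/L or pH < 7.0".

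The footnote on the register says "Diagnosis based on ICD codes or values (ml, kg, g, numbers" and points to an external variable list. Under Statistics and data analysis the article adds: "The secondary adverse neonatal and maternal outcomes will be analysed using the same type of methods and considerations as for the primary outcome".

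The article has no second definition of this outcome. It does not mention base deficit, BE is not in the abbreviation list, and no sign convention is given anywhere.

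**The concern.** Base excess is a signed quantity. A metabolic acidosis lowers it below zero; a value above +12 mmol/L is a large base surplus, which is the opposite of the condition named in the row. The footnote is an operative threshold and not background text: the row's method is a blood sample, not a diagnosis code, so the footnote is what turns recorded values into cases.

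The rule has two clauses. Any sample with pH < 7.0 qualifies by the second, so the first can add cases only where pH is at least 7.00 and below 7.05. If the first clause cannot be met there, it adds nothing and the outcome becomes pH < 7.0 alone. What is at stake is the group the first clause was evidently written to add: infants just above the lower pH cut with a substantial base deficit.

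**Working it through.** There is no stated figure to reproduce. The check is whether the first clause can be met as written, and whether it can be met once the sign is turned.

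**Inputs from the article:** the pH cuts 7.05 and 7.0 and the base-excess cut 12 mmol/L (Table 2, footnote g).

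**Inputs assumed:** standard acid-base constants, which the article does not give. Three forms of the base-excess equation are used to show the range:

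- Simple: BE = 0.93 × (HCO3 − 24.4 + 14.8 × (pH − 7.4))
- Extracellular fluid: BE = HCO3 − 24.8 + 16.2 × (pH − 7.4)
- Whole blood, haemoglobin assumed 10 mmol/L: BE = (1 − 0.023 × 10) × (HCO3 − 24.4 + (2.3 × 10 + 7.7) × (pH − 7.4))

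Bicarbonate is converted to pCO2 by pCO2 = HCO3 / (0.0307 × 10^(pH − 6.1)). At pH 7.05 the denominator is 0.0307 × 10^0.95 = 0.2736.

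**Step 1. The clause as written, BE = +12 at pH 7.05**

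- Simple: HCO3 = 12/0.93 + 24.4 + 14.8 × 0.35 = 12.9 + 24.4 + 5.2 = 42.5 mmol/L; pCO2 = 42.5/0.2736 = about 155 mmHg (20.7 kPa)
- Extracellular: HCO3 = 12 + 24.8 + 16.2 × 0.35 = 42.5 mmol/L; pCO2 about 155 mmHg
- Whole blood: HCO3 = 12/0.77 + 24.4 + 30.7 × 0.35 = 15.6 + 24.4 + 10.7 = 50.7 mmol/L; pCO2 about 185 mmHg (24.7 kPa)

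At pH 7.00, the lower edge of the band, the required pCO2 rises to about 177–214 mmHg.

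**Step 2. How far ordinary values lie from that**

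- Even BE = 0 at pH 7.05 needs a pCO2 of about 108–128 mmHg across the three forms.
- For pCO2 from 50 to 100 mmHg at pH 7.05, BE runs from −14.8 to −2.1 (simple) or −16.8 to −3.1 (extracellular). It is negative throughout.

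The first clause is therefore practically empty in the only pH band where it could add cases.

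**Step 3. The clause with the sign turned, BE = −12 at pH 7.05**

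| Form | HCO3 (mmol/L) | pCO2 (mmHg) | pCO2 (kPa) |
|---|---|---|---|
| Simple | 16.7 | 61 | 8.1 |
| Extracellular | 18.5 | 68 | 9.0 |
| Whole blood | 19.6 | 71 | 9.5 |

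Samples at this pH with a pCO2 below these values have a deficit above 12 mmol/L. The clause can then be met and adds cases beyond pH < 7.0.

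**Step 4. Whether bracketing matters**

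It does not. Every sample with pH < 7.0 also has pH < 7.05, so grouping the two conditions joined by *and*, or the two joined by *or*, selects the same samples. The sign is the only defect in the rule's logic.

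**The case against.** The strongest reply is that nobody would be misled. The row is named metabolic acidosis, so a base figure of 12 beside a pH below 7.05 can sensibly mean only a deficit of that size, and a programmer would probably notice a clause that selects no one. The register may also hold the value as an unsigned deficit, in which case the footnote works as written. The register footnote allows diagnosis codes as well as values, and Table 2 uses the word calculated only for small for gestational age, so derivation from blood-gas values is itself an inference, though a natural one. All of this stands, and it makes the loss of cases conditional. It does not make the text right: the article neither says deficit nor gives the register's convention. A minus sign lost in typesetting would not explain it either, because a threshold of BE above −12 also points the wrong way.

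Three stronger readings are tempting, and the article does not support them.

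- A reader might infer that the trial will in fact miss every infant in the pH band 7.00 to below 7.05 who has a large deficit. That follows only from literal coding on signed values, which the article does not establish.
- A reader might want to put a percentage on the lost events and convert it into lost precision. The article has no cord-gas distribution, so any share would be a guess. Precision would also depend on the clustering by centre that the planned models allow for, and not on the event count alone.
- A reader might blame the sign for an outcome that does not separate metabolic from respiratory acidosis. That feature comes from the pH < 7.0 clause, which has no base criterion and stays unchanged after the correction.

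**Conclusion.** Footnote g is wrong as written: it defines an acidosis by a positive base excess. This is an error in a stated case definition, not a detail left to a fuller document. Read literally on signed values, the first clause is practically never met (pCO2 of about 155–185 mmHg or more at pH 7.05, depending on the formula) and the outcome reduces to pH < 7.0. The conclusion about the sign rests only on what base excess means. The near-emptiness of the clause rests on standard constants, and all three forms agree on it.

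The practical effect depends on how the register records base excess and on how the analyst codes the rule, neither of which the article shows, so the number of cases at risk cannot be computed. The scope is one secondary neonatal outcome. Large for gestational age, the sample size and the primary model are untouched. It is a small correction, but worth making because the rule decides who counts as a case.

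**What to change.** Restate footnote g as: pH < 7.0, or pH < 7.05 together with a base deficit above 12 mmol/L (that is, BE < −12 mmol/L). Add base excess to the abbreviation list with its sign convention. Before deriving the outcome, confirm in the register's variable list, and by looking at the recorded values, whether base excess is stored signed or as an unsigned deficit, and code the inequality to match.

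The cost is one line in the outcome definition and one check of the variable. No design, sample-size or model change follows.
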